### Adverse events/serious adverse events

Subjects will be encouraged to report adverse events at each treatment session using the TESS-adverse event form. For serious adverse events such as death, life threatening events, significant or persistent disability/incapacity, hospitalization or prolongation of existing hospitalization, the date, time, vital signs and reasons for treatment assignment disclosure should be noted in the Severe Adverse Event (SAE) Form, reported to the Institutional Review Board (IRB) and monitored within 48 h. If there are medical concerns such that the treatment protocol has to be revised due to safety, sudden serious adverse events or ethical reasons, the revision must be approved by the IRB before implementation. If a subject withdraws from the study, the reasons for withdrawal will be recorded.

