### Interventions

#### Sinew acupuncture group

Subjects receiving sinew acupuncture will sit on a chair with the knee joint flexed at a most comfortable angle as close to 90 degrees as possible (if required, a block of A4 papers will be placed under the foot to adjust the angle). A hospital trolley table will be set up to block the vision of the subject to his/her knee (for blinding purposes). Routine disinfection will then be performed by the acupuncturist with a 75% alcohol pad. Acupoints (1–2 cm away from the point of tenderness, spasm or pain) along the meridian sinews near the knee(s) will be punctured through the skin by using sterile needles with a size of 0.30 mm × 40 mm (MOCM®) at an angle of 0–10 degrees pointing along the direction of the pain and the meridian sinew. The needles will be withdrawn immediately to a depth just under the skin and inserted forward smoothly 10 mm to 20 mm to avoid inducing pain. Five to eight points will be selected on each painful knee (while walking and climbing stairs) based on the theory of sinew acupuncture. Adjustments of the needles will be performed by extension and flexion of the knee joint to ensure that the needles do not cause pain during movement. Needles will be covered immediately by hypoallergenic bandages. The trolley table will be pulled away. Subjects will be advised to walk for 10 min (including the needle adjustment time). Needles will be adjusted at any time during walking if the subject has any pain induced by the acupuncture needle (for safety purposes) or primary pain of KOA (for the purpose of enhancing treatment effect). The trolley table will be used for blinding when the acupuncturist adjusts the needles. The acupuncturist will record the details of every adjustment procedure. After 10 min of walking, patients will be advised to step up and down from a step (~ 18 cm in height) for 12 rounds per knee. The pain points will be examined, and needle adjustments will be performed if necessary, followed by a period of rest by sitting for 5 min. After treatment, the needles will be removed while the subject is in a sitting position with the trolley table in place for blinding. Bandages will be applied in the same position for continuous blinding. The entire procedure will last 30 min per session. Subjects will receive 10 sessions of interventions for 4 weeks, starting with thrice a week during the first 2 weeks and then twice a week during the last 2 weeks. The above procedures will be performed by the acupuncturist and blinded to subjects.

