### Potential risks and management

During the treatment, all acupoints will be located around the knee joint(s), and the needle insertion will be superficial/subcutaneous with standardized disinfection procedures. This method has very low risks of infection, pneumothorax or perforation of the viscera.

Small amounts of bleeding or bruising may occasionally occur. In clinical experience, a small amount of bleeding can be stopped by applying pressure with sterile cotton swabs/balls. Bruises usually disappear within 2–3 days.

A step test is used to evaluate the subjects’ pain points while ascending/descending steps. To avoid falls, the step will be placed near a treatment bed, and a clinical assistant will accompany the subject at all times. The stairwell on the same floor of the hospital equipped with handles, bright lighting and anti-slip coating will be used for SCT assessment. Assessors will accompany the subjects during TUG and SCT assessments.

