## Discussion

KOA is one of the most common diseases among the elderly. This study will evaluate the efficacy of sinew acupuncture for pain reduction, functional movement improvement, and QOL improvement in KOA patients. In our clinic, there are 8–10 new KOA patients each month. We estimate that recruitment will be completed in 10 months.

The study is conducted in collaboration with the School of Chinese Medicine, Department of Diagnostic Radiology and Department of Orthopaedics & Traumatology, Li Ka Shing Faculty of Medicine, HKU. The eligibility of KOA subjects will be assessed by clinical physicians. The intervention will be performed by experienced acupuncturists. The subjects and assessors will be blinded to subjects’ allocations. The acupuncturist will not be involved in assessments or data entry. Data will be analysed by an independent statistician.

In acupuncture RCTs, it is critical to choose an appropriate control population. Vickers AJ et al. found that acupuncture was superior to both sham and no acupuncture controls for osteoarthritis pain with effect sizes of 0.16 and 0.57, respectively [18]. The small effect size in trials with sham acupuncture controls may be due to the following reasons: (1) the meta-analysis excluded outlying studies showing a very large effect size [18] and (2) according to Macpherson H, Vickers AJ, et al. in the same research group, acupuncture has a smaller effect size in trials with needle-insertion sham controls than in trials with needle non-insertion sham or non-sham controls [15]. Our previous study was consistent with their findings that acupuncture trials with needle non-insertion controls lead to more positive conclusions than those with needle-insertion sham controls [16]. In the present study, we will use needle non-insertion as the control, which may produce a smaller, nonspecific effect compared to needle-insertion sham controls. However, it should be noted that the effect size estimated from our pilot study [29] is larger than that of the previous study by Vickers AJ et al. [18]. If the power estimates prove to be high, the trail can be used to determine a more accurate effect size for future power calculations.

This trial will expand our knowledge of whether sinew acupuncture will reduce pain intensity, improve the symptoms and movements of KOA patients, and improve QOL. If this study is successful, the effectiveness of sinew acupuncture may be studied using a pragmatic trial design.

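### Non-serious adverse events come only from subject report, while blinding hides the needle sites from the subject, so minor penetration harms may be missed, mainly in the sinew arm

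*Protocol article*

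**What the plan says.** All places are in the protocol article.

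- **Aim.** The Background says that safety will be evaluated and hypothesises that sinew acupuncture works safely compared with sham.
- **Collection.** Under Adverse events/serious adverse events: "Subjects will be encouraged to report adverse events at each treatment session using the TESS-adverse event form". Serious events have their own form and reporting path. Table 1 ticks adverse events at all 10 sessions and at weeks 6 and 10.
- **Screening of the knee.** Under Sinew acupuncture group: "A hospital trolley table will be set up to block the vision of the subject to his/her knee (for blinding purposes"). Once the needles are in, "Needles will be covered immediately by hypoallergenic bandages", and then "The trolley table will be pulled away". The table returns for adjustments and for removal, after which "Bandages will be applied in the same position for continuous blinding".
- **Needle pain.** The same section says: "Needles will be adjusted at any time during walking if the subject has any pain induced by the acupuncture needle (for safety purposes"). Adjustments are also made for the primary knee pain, to enhance the treatment effect. The acupuncturist records the details of each one.
- **Named harms.** Under Potential risks and management: "Small amounts of bleeding or bruising may occasionally occur". Bruises are said to clear in 2–3 days.
- **Sham arm.** The procedures are the same, except that the needle is not meant to go through the skin (Sham acupuncture group).
- **The acupuncturist's record.** Outcome measures describes a Physical Examination and Treatment Form covering history, diagnosis and what was done. Table 1 ticks it at baseline, every session and both follow-up visits. The Discussion adds: "The acupuncturist will not be involved in assessments or data entry".

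**The concern.** The stated method of collecting harms and the stated method of blinding pull against each other. The subject is the only named source for non-serious events, and the procedure is built so that the subject does not see the needle sites. The person who does see them, the acupuncturist, has a form at every session, but its described content does not include adverse events. The harms at issue come from skin penetration, which only the sinew arm is meant to have. At stake is the absolute excess of minor local harms under sinew acupuncture, which a trial with a comparative safety hypothesis should be able to report.

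**Working it through.** The article gives no adverse-event rate, capture rate or safety power, so there is no figure of its own to reproduce. The check sets the passages side by side, harm by harm.

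| Harm | Can the subject perceive it? | Does the acupuncturist meet it? | Stated path to the adverse-event record |
|---|---|---|---|
| Small bleed at removal | Not by sight: table in place, then bandage | Yes | Subject report only |
| Bruise | Possibly later; how long bandages stay on is not stated | Possibly, at the next session | Subject report, at a session or follow-up visit |
| Needle pain leading to adjustment | Yes, it is felt | Yes, and each adjustment is recorded | Subject report only; adjustment record not linked |
| Bent or broken needle | Not by sight | Yes; needles are also counted (Safety) | Subject report only |

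**Bruise timing.** Sessions run three a week for two weeks, then two a week for two weeks. The average gap is 7/3 = 2.3 days, then 7/2 = 3.5 days. Against a duration of 2–3 days, some bruises will still be visible at the next session and some will have faded. Subjects may also see them at home. Some loss is plausible; complete loss is not.

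**Exposure.** With 43 subjects per arm and 10 sessions, each arm has 43 × 10 = 430 sessions. At 5 to 8 points on one painful knee, that is 430 × 5 = 2,150 to 430 × 8 = 3,440 needle placements per arm, and twice that if both knees are painful.

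**What incomplete capture does to the comparison.** Observed risk = true risk × share captured. All rates below are assumptions: true per-subject risk of a local harm 10–50% sinew and 2–5% sham; share captured 40–70%, equal in both arms; 43 per arm.

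- Missed subjects, sinew: from 43 × 0.10 × 0.30 = 1.3 to 43 × 0.50 × 0.60 = 12.9.
- Missed subjects, sham: from 43 × 0.02 × 0.30 = 0.3 to 43 × 0.05 × 0.60 = 1.3.

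| True risk, sinew v sham | True difference | Difference at 70% capture | Difference at 40% capture | Risk ratio throughout |
|---|---|---|---|---|
| 10% v 2% | 8 points | 5.6 | 3.2 | 5.0 |
| 30% v 5% | 25 points | 17.5 | 10 | 6.0 |
| 50% v 5% | 45 points | 31.5 | 18 | 10.0 |

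With equal capture, the absolute difference shrinks by the capture share and the ratio does not move. The ratio moves only if capture differs between arms: 30% v 5% with 40% capture in the sinew arm alone gives 12% v 5%, a ratio of 2.4. Nothing in the article shows that this would happen.

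**The case against.** The strongest reply is that this is a missing cross-reference in a condensed article, and that the routes already described would catch most of these events.

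- The table is pulled away for walking, so the view is not blocked throughout. Bruises can be seen later. Table 1 also collects adverse events at weeks 6 and 10. This stands, and it limits the point on bruising.
- Needle pain is felt, and every adjustment is recorded. This stands: needle pain is not lost. What remains is that the record is not tied to adverse events, and that adjustments for needle pain and for knee pain are both counted as adjustments. A bare count would mix a harm with a treatment step.
- The acupuncturist completes a form at every session, and the Discussion's exclusion from assessments most naturally refers to outcome assessment. It does not bar noting a harm. This also stands, but no passage gives the acupuncturist that duty.
- The full protocol may settle who records what. It may, and in that case the fix is already in place. The article does more than stay silent, however: it names one reporter and a procedure that hides the sites from that reporter.

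A reader might infer that assessors complete the adverse-event form and would be unblinded by a bleed or bruise. The article does not say who takes the form, so this is a possibility to guard against and not a finding.

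**Conclusion.** As written, the collection method can miss small bleeds and some bruises, and it leaves needle pain outside the adverse-event record unless the subject also reports it. Such losses would fall mainly in the sinew arm, because penetration harms arise mainly there, and may shrink the absolute between-arm difference in harms. The size is unknown. The ranges in the working show how the arithmetic behaves under assumed rates and are not estimates for this trial.

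A reader might go further and conclude that harms will certainly be undercounted, or that the safety comparison is biased toward no difference. The documents support neither. No event or capture rate is given, and the table and bandages are used in both arms. More missed events in the arm with more events is not differential capture, and under equal capture the risk ratio is preserved. The point is a gap in ascertainment that is cheap to close. It does not bear on the primary VAS comparison.

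**What to change.** In the Adverse events/serious adverse events section, add that the acupuncturist completes a fixed yes/no list at needle removal, in every session and in both arms, on the existing Physical Examination and Treatment Form. The items are:

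- bleeding;
- visible bruising;
- adjustment because of needle-induced pain, kept distinct from adjustment for knee osteoarthritis pain;
- fainting;
- bent or broken needle;
- in the sham arm, unintended skin penetration.

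Tabulate these counts by arm next to the subject-reported events but separately from them, and keep the form from the blinded outcome assessors.

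The cost is a short tick-list on a form already completed at every session, and a sentence or two of protocol text. It needs no extra staff and changes no treatment rule. The one drawback is that the recorder knows the allocation, which is why the two sources should be shown separately and not pooled.

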### Safety

Either sinew acupuncture or sham acupuncture will be performed by registered acupuncturists in Hong Kong who have at least 3 years of acupuncture experience. Throughout the trial, acupuncturists will follow the guideline from the Hong Kong Hospital Authority on Safety in Acupuncture for Chinese Medicine Practitioners (2nd amended version, 2016) including (1) prevention of fainting and syncope during acupuncture; (2) prevention of bleeding and bending or breaking of needles during acupuncture; and (3) prevention of performing acupuncture on the skin with local infections, ulcers, scars, or tumour. All acupuncture procedures adopted in our clinic (The Hong Kong Tuberculosis Association Chinese Medicine Clinic cum Training Centre of the University of Hong Kong) will follow (1) the introduction of the Notice for Patients Receiving Acupuncture and Tui-na Treatment at their first visit and (2) implementation of needle counting before and after each acupuncture session.

Adhesive bandages will consist of a flexible, non-woven, low-adherence contact layer and a low-allergy, acrylic adhesive backing layer, which will be used to maintain the needle position during movement.

### Potential risks and management

During the treatment, all acupoints will be located around the knee joint(s), and the needle insertion will be superficial/subcutaneous with standardized disinfection procedures. This method has very low risks of infection, pneumothorax or perforation of the viscera.

Small amounts of bleeding or bruising may occasionally occur. In clinical experience, a small amount of bleeding can be stopped by applying pressure with sterile cotton swabs/balls. Bruises usually disappear within 2–3 days.

A step test is used to evaluate the subjects’ pain points while ascending/descending steps. To avoid falls, the step will be placed near a treatment bed, and a clinical assistant will accompany the subject at all times. The stairwell on the same floor of the hospital equipped with handles, bright lighting and anti-slip coating will be used for SCT assessment. Assessors will accompany the subjects during TUG and SCT assessments.

### Ethics and dissemination

The ethical validity of the study has been assessed and approved by the Institutional Review Board of The University of Hong Kong/Hospital Authority Hong Kong West Cluster (HKU/HA HKW IRB, approved number UW 16–2007). The study was registered on ClinicalTrials.gov (Identifier: NCT03099317). The clinical study will be overseen by the HKU/HA HKW IRB. All subjects will receive sufficient information about the trial and must sign the informed consent form prior to enrolment. Case repot forms (CRFs) and study files will be archived for 3 years after completion of the final report and locked in a research cabinet. The Personal Data (Privacy) Ordinance (CAP 486) will be followed strictly.

### Sample size estimation

G-power was used for sample size determination. The sample size was estimated by the VAS value with sinew acupuncture for knee pain using data from our pilot study [29]. The study observed 85 sessions of acupuncture treatments on the knee. After acupuncture treatments, the average VAS was reduced from 38.9 to 21.0 (change = − 17.9) with a standard deviation = 10.7. We estimated that the sham acupuncture (17.9*60% = 10.74) could reduce 60% of pain intensity compared to true acupuncture. The effect size was 0.673. With α = 0.05 and power (1-β) =0.8, the sample size was determined to be 37 per group. With the consideration of a 15% dropout rate, 86 subjects are required in each of the two groups.

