**Methods/design:**

A randomized, sham-controlled, patient- and assessor-blinded trial will be conducted to compare the efficacy of sinew acupuncture and sham acupuncture. Subjects will be assessed by the physician and acupuncturists. A sample of eighty-six eligible subjects will be randomized into either the sinew acupuncture group or the sham acupuncture group. The intervention will be performed in the Hong Kong Tuberculosis Association Chinese Medicine Clinic cum Training Centre of the University of Hong Kong by acupuncturists with over 3 years of acupuncture experience. Subjects will receive 10 sessions of interventions for 4 weeks, followed by a 6-week follow-up. The visual analogue scale (VAS) score at week 4 will be the primary outcome. The Western Ontario and McMasters University Osteoarthritis Index (WOMAC), Timed Up & Go Test (TUG), 8-step Stair Climb Test (SCT) and the 36-Item Short Form Survey (SF-36) will be secondary outcomes.

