### Exclusion criteria

Subjects will be excluded if they meet any of the following criteria: (i) are unable to walk; (ii) have a serious infection of the knee; (iii) have suspected tears in any ligaments or menisci or acute inflammation of the synovial capsule; (iv) have a history of trauma, ligament damage, fracture, or surgery on the knee(s) within 6 months, causing pain or functional problems (history of knee replacement will be excluded); (v) have a history of local tumour/malignancy at the knee; (vi) have physical or laboratory findings indicating infection, presence of autoimmune disease or inflammatory arthritis; (vii) have knee pain caused by radiculopathy/herniation of an intervertebral disc; (viii) have end-stage diseases or other suspected severe conditions such as deep vein thrombosis of the lower limb, oedema related to cancer or cancer treatment, severe blood coagulation disorders, uncontrolled systemic arterial hypertension and severe diabetes; (ix) have a history of prolotherapy, hyaluronic acid injections or corticosteroids injections within 3 months; (x) have received acupuncture, electro-acupuncture, Tui-na therapy, massage, or physiotherapy 8 weeks prior to enrolment in the trial; (xi) have severe pain in other regions; (xii) have severe mental disorder(s); (xiii) are oversensitive to needles; and (xiv) are insensitive to pain due to advanced diabetes, neuropathy or use of strong painkillers.

Eligible subjects will receive baseline assessments and will be randomly allocated to the sinew acupuncture group (*n* = 43) or the sham acupuncture group (*n* = 43) in a ratio of 1:1 by block randomization. The random digits and letters will be generated by SPSS, covered by aluminium foil, and sealed into opaque envelopes.

Subjects will be advised not to receive other acupuncture treatments, Tui-na, massage or physiotherapy. Subjects are not restricted from the use of painkillers (including herbs) or external ointments if they suffer intolerable pain. The use of rescue medications, the daily level of morning stiffness and exercise time will be recorded in patient diaries.

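### The sample-size section requires 86 subjects in each group, but the design randomises 86 in total (43 per group), and the section's own inputs support only the total.

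*Protocol article*

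**What the plan says.** The Sample size estimation section works from pilot data on the knee: "the average VAS was reduced from 38.9 to 21.0 (change = − 17.9) with a standard deviation = 10.7". Sham is assumed to achieve 60% of that change: "We estimated that the sham acupuncture (17.9*60% = 10.74) could reduce 60% of pain intensity compared to true acupuncture". It then reports "The effect size was 0.673" and "With α = 0.05 and power (1-β) =0.8, the sample size was determined to be 37 per group". Its last sentence reads: "With the consideration of a 15% dropout rate, 86 subjects are required in each of the two groups".

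Two other places give the size of the trial:

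- **Abstract, Methods/design:** "A sample of eighty-six eligible subjects will be randomized into either the sinew acupuncture group or the sham acupuncture group".
- **Allocation paragraph, at the end of Exclusion criteria:** n = 43 for the sinew group and n = 43 for the sham group, allocated "in a ratio of 1:1 by block randomization".

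The Discussion adds a forecast of 8–10 new knee osteoarthritis patients a month at the clinic, with recruitment complete in 10 months.

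**The concern.** The sample-size section asks for 2 × 86 = 172 subjects. The Abstract and the allocation paragraph provide for 86. Both are current statements of the same quantity, and the wording of the sample-size sentence cannot be read as a total.

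The required sample size is a figure against which the finished trial will be judged. A reader who goes only to the sample-size section would conclude that a fully recruited trial of 86 had reached 86/172 = 50% of its target. The same reader could not match the 80% power claim to the number of subjects given.

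**Working it through.** **Inputs** (Sample size estimation, except sidedness, which is in Data analysis)

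- Change with sinew acupuncture: 38.9 − 21.0 = 17.9 mm
- Assumed change with sham: 0.60 × 17.9 = 10.74 mm
- Difference: 17.9 − 10.74 = 7.16 mm
- SD: 10.7
- Stated effect size: 0.673
- Two-sided α = 0.05, power 0.80, allocation 1:1
- Dropout: 15%

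**Step 1: effect size.** d = difference / SD = 7.16 / 10.7 = 0.669. The stated 0.673 would need an SD of 7.16 / 0.673 = 10.64. The gap is small, and both values are carried below.

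**Step 2: the plan's 37 per group.** Two-sample t-test, solved with the noncentral t distribution:

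| d | n per group for 80% power | Rounded up |
|---|---|---|
| 0.669 | 36.04 | 37 |
| 0.673 | 35.64 | 36 |

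The 37 reproduces from the mean difference and SD, and is one above the result from the stated effect size. A one-sided test would need only 28 to 29 per group, so the 37 belongs to a two-sided test.

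**Step 3: the dropout allowance.** Two conventions are in use:

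| Formula | Per group | Total |
|---|---|---|
| n × (1 + 0.15) | 37 × 1.15 = 42.55, so 43 | 2 × 43 = 86 |
| n / (1 − 0.15) | 37 / 0.85 = 43.53, so 44 | 2 × 44 = 88 |

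The first reproduces both the 43 per arm and the 86 in total. Neither gives 86 per group. To go from 37 to 86 per group, the allowance would have to be 1 − 37/86 = 57%.

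**Step 4: power under each reading.** After 15% loss, 43 per group leaves 43 × 0.85 = 36.55, and 86 per group leaves 86 × 0.85 = 73.1.

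| n analysed per group | Power, d = 0.669 | Power, d = 0.673 |
|---|---|---|
| 36 | 79.9% | 80.4% |
| 37 | 81.0% | 81.5% |
| 43 (no loss) | 86.6% | 87.0% |
| 73 | 98.0% | 98.1% |
| 86 (no loss) | 99.2% | 99.2% |

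The stated 80% goes with 43 randomised per group. It does not go with 86.

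**Step 5: recruitment.** Ten months at 8–10 patients a month gives 80–100. That covers 86. Enrolling 172 at the same rate would take 172/10 = 17.2 to 172/8 = 21.5 months. This is supporting evidence only, because the article also plans to recruit from nursing homes and community centres.

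**The case against.** The strongest reply is that this is a slip of wording which the article itself resolves. The same section derives 37 per group one sentence earlier, and 15% cannot turn 37 into 86. The Abstract, the two arm sizes and the recruitment forecast all point to 86 in total. Design, allocation, analysis and power are untouched, so the consequence is an erratum and no subject is enrolled or lost because of it.

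Most of that stands. The trial is not underpowered on its own assumptions, and it would be wrong to say that it enrols half of what its calculation needs. Only the concluding sentence makes that demand. A careful reader can also work out what was meant. But the sentence is still wrong as printed, in the place where a reader looks for the target, and the article nowhere corrects it.

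Two smaller points are fair. The sentence already includes dropout, so the like-for-like power for 86 per group is the 98% after loss, not the 99% with none. And Data analysis specifies intention to treat with the last observation carried forward, so some who drop out would still contribute a value. The 36 to 37 per group is then the number with week-4 data under the stated dropout, not necessarily the number analysed. Neither point changes the conclusion.

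**Conclusion.** The concern holds. The per-group figure in the Sample size estimation section is too large by a factor of two: 86 instead of 43 per group, or 172 instead of 86 in total. The Abstract and the allocation paragraph are consistent with the calculation, and the concluding sentence of the sample-size section is not.

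This rests on the article's own assumptions: a difference of 7.16 mm, SD 10.7, a two-sided 5% test, 80% power and 15% dropout. It does not depend on whether 0.669 or 0.673 is used, or on which dropout convention is applied, since the per-group result is 43 or 44 either way. Whether the pilot effect size is realistic is a separate question and is not judged here.

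**What to change.** Correct the last sentence of Sample size estimation so that it requires 43 subjects in each group, 86 in total, in agreement with the Abstract and the allocation paragraph. Add that 15% dropout from 43 leaves about 36 subjects per group (36.55), which gives about 80% power under the stated assumptions. This addition is not essential, but it lets a reader tie the size to the power.

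If the intention is to keep a full 37 per group after 15% loss, 37 / 0.85 calls for 44 per group (88 in total). The difference is one subject per arm and the choice is one of convention. Keeping 43 is acceptable if the sentence says what it leaves.

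The cost is one corrected sentence, with no change to enrolment, allocation or analysis.
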